### Data management

#### Data collection

All the information should be honestly and precisely recorded in a timely manner in the case report form (CRF) or CRF software. Researchers are required to record the patients’ information in the CRF according to the program of the trial. The research center will appoint supervisors to examine the completeness and accuracy of the CRF and to guide the researchers in making changes or additions if necessary. The CRF is submitted to data management by the region supervisor, with one copy remaining in the research center and the other one as a working attachment for the supervisor. Reliable data managers for medicine will input the data from the CRF to the database. The CRF should be filled in by a specific person assigned by the coordinating center and will not make sense until it is signed by the chief in the corresponding center. The center in charge will regularly check and collect the CRF in the coordinating centers. The database generated by software will be transmitted over the network to the center in charge.

At the end of the trial, each coordinating center should submit a summary of their own according to clinical summary standards. The leading center will arrange all the forms and make conclusions. An overall summary according to clinical summary standards is required.

#### Case report form

In the trial, observation or examination items need to be recorded in the CRF. The contents of the CRF should be identical to the original materials. In the CRF, the results calculated from the original materials should be able to be back-dated.

The CRF must be filled in with the following criteria satisfied:Use black pen or black ball-point pen to fill in data.Data from patients who have signed informed consent and met inclusion criteria, but who are subsequently judged to fail to meet inclusion criteria after treatment or even without drug treatment, should be recorded in the CRF.Draw on the original record with horizontal lines when making corrections (correction fluid is not allowed). Make sure the original record is identifiable and then sign and date the correction.For items not yet examined, “ND” should be marked in the CRF.

#### Database management and quality control

Measures are taken to achieve quality control. Data items of the CRF will be input into the database. Text items can only be checked manually at the first time they are input. Subsequently, data managers will systematically check the information in the database. The database will be locked when completed without errors. Any changes in the database can only be achieved with the joint written consent from clinical research leaders, statisticians, and data managers.

### Data analysis

#### Interim analysis

When the number of cases reaches 400, an interim analysis will be performed to identify any evidence of definite superiority of the experimental intervention. The interim report includes the following content:The number of the enrolled patients and the planned time for completionThe number of cases with compliance and non-complianceAssessment of quality of the materials according to the submission time, completeness, and accuracy of the materialsPreliminary analysis of treatment efficacy, including nutritional status, quality of life, and rate of complicationsIncidence and classification of adverse reactions

The central center will regularly report to all the coordinating centers according to the above information. If necessary, this study will be adjusted or terminated depending upon the results of the interim analysis.

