## Methods/design

### Trial design

This is a multi-center, prospective, phase III, randomized controlled trial, supported by the China Southern Gastric Cancer Cooperation (CSGC). The Sixth Affiliated Hospital of Sun Yat-sen University associated with the other eighteen hospitals in Southern China is responsible for this trial. Patients from the coordinating centers who satisfy the pre-specified criteria will be included and randomly divided into two groups: an experimental group undergoing uncut Roux-en-Y anastomosis and a control group undergoing Billroth II anastomosis. We will follow the patients after surgery to observe postoperative complications and nutrition status for 5 years. The study flow chart is shown in Fig. 2. An interim analysis will be undertaken when 400 eligible cases are enrolled, and we will subsequently evaluate whether the trial should be continued or terminated depending upon the results of the interim analysis. The example template of recommended content for the schedule of enrolment, interventions and assessments is shown in Fig. 3.

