### Sample size

Our study is designed as a superiority trial whose primary outcome is postoperative reflux gastritis or not. Current experience suggests the predicted rate of postoperative reflux gastritis will be 8% for the uncut Roux-en-Y anastomosis group and 12% for the control group of Billroth II anastomosis. The difference test was used to estimate the sample size with 80% test power and a 5% significance level. Accounting for a 15% drop-out rate and the 1:1 allocation ratio, the total number of patients required per group is 416 (832 in total), which was calculated using the software PASS version 11.0. Considering a completion rate of 75% for each coordinating center, 1040 envelopes were designed for random allocation. The number of cases will be increased if necessary according to the results of the interim analysis.

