#### Statistical analysis

Statistical analysis planning was formulated by health statisticians as well as key researchers. We will use SPSS or SAS to analyze the data. For survival analyses, Kaplan-Meier curves and log rank tests will be used. The Cox proportional hazards model will be used for prognosis analysis. Categorical variables will be analyzed by Pearson’s χ^2^ test or Fisher’s exact test, and continuous variables will be evaluated by Student’s *t*-test or an appropriate non-parametric method as required. The level of statistical significance will be set at 5%.

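### The superiority interim at 400 enrolled patients has no stated share of the single 5% level, is timed by enrolment, and its efficacy content is reported to every centre

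*Protocol article*

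**What the plan says.** All references are to the Protocol article.

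- **Purpose.** The Interim analysis section states: "When the number of cases reaches 400, an interim analysis will be performed to identify any evidence of definite superiority of the experimental intervention". This is a look for efficacy.
- **Trigger.** Trial design: "An interim analysis will be undertaken when 400 eligible cases are enrolled". The count is of enrolled patients, not of patients with a completed endoscopy.
- **Consequences.** Interim analysis: "If necessary, this study will be adjusted or terminated depending upon the results of the interim analysis". Sample size: "The number of cases will be increased if necessary according to the results of the interim analysis". No rule or cap for the increase is given.
- **Significance level.** Statistical analysis: "The level of statistical significance will be set at 5" per cent. Sample size: "The difference test was used to estimate the sample size with 80% test power and a 5% significance level". No other level appears, and the calculation is described as for one test.
- **Content.** The Interim analysis section lists a preliminary efficacy analysis covering nutrition, quality of life and complication rates. It does not name reflux gastritis, the outcome on which the Sample size section bases the trial.
- **Recipients.** Interim analysis: "The central center will regularly report to all the coordinating centers according to the above information". The information referred to includes the preliminary efficacy item.

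**The concern.** There are three distinct problems, and they should not be merged.

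1. **Error rate.** A look that can end the trial for superiority gives a second chance of a false positive. If the final test keeps the full 5%, the overall error is above 5%; how far above depends on the interim level, which is not stated. Raising the sample size after seeing a between-arm result can add to it.
2. **Reliability of the look.** Enrolment does not deliver endoscopic outcomes. The Elimination criteria section places the primary evaluation at six time points from 6 months to 5 years. A stop could therefore rest on early primary data or, going by the listed content, on outcomes other than reflux gastritis.
3. **Operational bias.** Centres that learn preliminary efficacy while still recruiting and following patients may change whom they approach or how they assess endoscopic findings. The Discussion itself calls blinding of surgeons and patients the most challenging aspect of the design.

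The second and third problems do not themselves raise type I error. They affect how far the result can be trusted.

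**Working it through.** **Inputs.** Interim at 400; planned total 832 (416 per group), 15% drop-out, 5% level, 80% power, and rates of "8% for the uncut Roux-en-Y anastomosis group and 12% for the control group of Billroth II anastomosis" (Sample size); enrolment over 3 years (Trial status).

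**The plan's own figure.** The stated 416 per group is not reproduced from these inputs. The normal-approximation formula gives 882 evaluable per group two-sided (1,038 with drop-out) or 695 one-sided (818 with drop-out). That is a separate matter. Here 832 is taken as the planned size; a larger trial would lower the information fraction and slightly raise the 5%-at-both-looks figures below.

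**Information fraction t.** 400/832 = 0.481. If the 400 are evaluable patients and the final analysis has 832 × 0.85 = 707, then t = 400/707 = 0.566.

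**Type I error over two looks.** The standardised statistics at the two looks are bivariate normal with correlation √t, so the overall two-sided error is 1 − P(|Z₁| < c₁ and |Z₂| < c₂).

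| Interim level | Final level | t | Overall error |
|---|---|---|---|
| 5% | 5% | 0.481 | 8.4% |
| 5% | 5% | 0.566 | 8.1% |
| 5% | 5% | 0.30 | 8.9% |
| 5% | 5% | 0.148 (123/832) | 9.4% |
| 0.0047 | 5% | 0.481 | 5.2% |
| 0.0025 | 5% | 0.481 | 5.1% |
| 0.001 | 5% | 0.481 | 5.02% |

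Sidedness is not stated; a one-sided 5% test at both looks gives 8.1% at t = 0.481. The row at t = 0.148 would need a 12-month primary time point, which the article does not fix.

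**Sample-size increase.** If the increase were driven without restriction by the between-arm result, the Proschan-Hunsberger worst case for one test at one-sided level α is α + exp(−z²/2)/4. For α = 2.5% this is 0.025 + 0.1465/4 = 6.2%; for α = 5% it is 0.05 + 0.2585/4 = 11.5%. These are upper bounds.

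**Maturity at the trigger.** Assuming uniform accrual, 832/36 = 23.11 patients a month:
- 400th patient: 400/23.11 = month 17.3.
- Reached 6 months: (17.3 − 6) × 23.11 ≈ 261, or 65% of 400.
- Reached 12 months: (17.3 − 12) × 23.11 ≈ 123, or 31% of 400.
- Reached 24 months: none.

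**Boundary that holds 5%.** With O'Brien-Fleming-type spending and 0.025 per side, the two-sided interim level is 4[1 − Φ(2.2414/√t)], and the final level is solved so that the overall error is 5%.
- t = 0.481: interim p < 0.0025, final p < 0.049.
- t = 0.566: interim p < 0.006, final p < 0.048.

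**The case against.** The strongest reply is that the article nowhere says the interim test uses p < 0.05. It asks for superiority that is definite, the 5% closes a general list of tests and can be read as the overall level, and a boundary may well stand in an analysis plan that is not shown. This stands. A reader might infer that both looks use 5% and that type I error therefore exceeds 5%; the document does not support that as fact, and 8.4% is one scenario.

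Other stronger readings also fail:

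- **That most of the 400 lack a primary outcome.** About 65% would have passed the first primary time point.
- **That the interim ignores reflux gastritis.** The efficacy list is open-ended, and complications could be meant to cover it. What can be said is that the outcome is not named. If it is not tested at the interim, the 8% figure does not apply either.
- **That unblinded endoscopists will see the results.** The blinding of endoscopists is not described.
- **That the sample size will be raised on the between-arm difference.** The text says only that it depends on the interim results; a pooled rate is not excluded.
- **That results go out by arm.** This is not stated, although an efficacy analysis seeking superiority is naturally comparative.

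The Randomization section also keeps allocation hidden until the gastrectomy is done, so interim knowledge cannot steer assignment. It could still affect recruitment and assessment.

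A boundary held elsewhere would settle the first problem. It would not change the enrolment trigger or the reporting to centres, which the article itself fixes.

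**Conclusion.** The point holds in conditional form. The protocol commits to a superiority look that can stop, adjust or enlarge the trial and gives one undivided 5% level. If 5% is applied to the primary outcome at both looks, type I error is about 8%. With an O'Brien-Fleming-type interim level at t = 0.48 and the final test left at 5%, it is 5.1% to 5.2%: above the nominal level, but little. Which applies cannot be told from the article. The calculation assumes the same outcome is tested at both looks and information proportional to patient numbers.

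Independently of that, the enrolment trigger gives a look with early primary data (the counts rest on uniform accrual of 832 over 36 months), and the reporting rule as written sends preliminary efficacy to centres still enrolling and assessing patients. Both should be changed whatever boundary is in use.

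**What to change.** - **Boundary.** Base any efficacy stop on reflux gastritis alone, with a named O'Brien-Fleming-type spending function computed at the actual fraction of evaluable patients. With 0.025 per side this means, for example, interim p < 0.0025 and final p < 0.049 at t = 0.48, or interim p < 0.006 and final p < 0.048 at t = 0.57. State sidedness. The thresholds depend on the spending form, so the form must be fixed in advance.
- **Trigger.** Define the look by the number of patients with the primary endoscopy, and say which scheduled endoscopy that is.
- **Sample size.** Allow an increase only from the pooled event rate.
- **Reporting.** Send centres enrolment, compliance, data quality and pooled safety only. Keep between-arm efficacy with the trial statistician and those who take the stop/continue decision.
- **If the look has already been taken,** record what was tested, at what level and who saw it, and set the final level accordingly.

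**Cost.** Mainly wording, and a final threshold slightly below 0.05. The real cost is timing. Allowing 15% drop-out, 400 evaluable patients need 400/0.85 = 471 enrolled, reached at month 20.4. Four hundred six-month endoscopies are then available near month 26, with about 609 enrolled; twelve-month ones near month 32, with about 748 of 832 enrolled. A stop that late spares few patients. The spending function also permits a smaller trigger, at a stricter interim level.

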#### Statistical analysis

Statistical analysis planning was formulated by health statisticians as well as key researchers. We will use SPSS or SAS to analyze the data. For survival analyses, Kaplan-Meier curves and log rank tests will be used. The Cox proportional hazards model will be used for prognosis analysis. Categorical variables will be analyzed by Pearson’s χ^2^ test or Fisher’s exact test, and continuous variables will be evaluated by Student’s *t*-test or an appropriate non-parametric method as required. The level of statistical significance will be set at 5%.

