### Trial objectives

The objectives of this trial are as follows:To test the hypothesis that uncut Roux-en-Y anastomosis can reduce postoperative complications and improve nutritional status for gastric cancer patients after D2 gastrectomy compared to Billroth II anastomosisTo provide class-one evidence for the reconstruction of distal gastrectomy

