### Outcome measures

All patients enrolled in this trial will be followed up regularly at stated intervals after the surgery for an average of 5 years. During the follow-up visits, patients will undergo endoscopy, laboratory tests, and radiography if necessary as described in Table 1.

**Table 1 Tab1:** Summary of the follow-up visit schedule and assessed parameters at each time point

	Preoperative	3 M	6 M	9 M	12 M	18 M	24 M	36 M	48 M	60 M
Endoscopy	*	**	*		*		*	*	*	*
Laboratory	*	*	*		*		*	*	*	*
CT scan	*	*	*		*		*	*	*	*
Upper digestive tract radiography	**	*	*		*		*	*	*	*

*Evaluation at the designated time point, **evaluation if necessary

The primary assessment indices of the study are reflux gastritis, esophagitis, bile regurgitation, and anastomotic ulcer. Endoscopy will be used to help with standardized assessment of these indices during the follow-up visits. Full details for the Los Angeles classification of the severity of reflux esophagitis are shown in Table 2.

**Table 2 Tab2:** Los Angeles classification of the severity of reflux esophagitis

Grade	Manifestation
A	One (or more) mucosal break(s) no longer than 5 mm that does not extend between the tops of two mucosal folds
B	One (or more) mucosal break(s) more than 5 mm long that does not extend between the tops of two mucosal folds
C	One (or more) mucosal break(s) that is continuous between the tops of two or more mucosal folds but which involve(s) less than 75% of the circumference
D	One (or more) mucosal break(s) that involve(s) at least 75% of the esophageal circumference

The secondary assessment indices are nutritional status, quality of life, perioperative complications, overall survival rate, and others. Nutritional status includes body mass index (BMI), hemoglobin, albumin, total protein, pre-albumin, transferring, and other indices such as appetite and Onodera’s prognosis nutritional index (PNI). Quality of life will be assessed by the gastrointestinal symptom rating scale (GSRS) and Visick score (shown in Additional file 1: Tables S1 and S2). Perioperative complications occurring within 30 days after the surgery include anastomotic fistula and anastomotic stenosis. Overall survival rates for 1, 3, and 5 years after the surgery as well as recurrence and metastasis rates will be calculated. Other indices include surgery time, intraoperative blood loss, length of hospital stay, and hospital cost.

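### The laboratory nutritional outcomes are compared with no baseline term although preoperative laboratory tests are scheduled; this costs precision on secondary outcomes but does not cause bias

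*Protocol article*

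**What the plan says.** In the protocol article, the Statistical analysis section assigns tests by type of variable. For continuous outcomes it says that "continuous variables will be evaluated by Student"'s t-test "or an appropriate non-parametric method as required". It names no covariate, baseline term or change score for them. The only regression model in that section is the Cox model, for prognosis.

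Trial objectives gives the hypothesis as "uncut Roux-en-Y anastomosis can reduce postoperative complications and improve nutritional status for gastric cancer patients after D2 gastrectomy", with Billroth II as comparator. Outcome measures ranks nutrition lower: "The secondary assessment indices are nutritional status, quality of life, perioperative complications, overall survival rate, and others". It then lists the components: "Nutritional status includes body mass index (BMI), hemoglobin, albumin, total protein, pre-albumin, transferring, and other indices such as appetite". Most of these are continuous laboratory values.

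Table 1 marks the laboratory row as a designated assessment, not an optional one, preoperatively and at 3, 6, 12, 24, 36, 48 and 60 months. The row does not list the analytes, and the table has no row for BMI or appetite.

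**The concern.** A patient's hemoglobin or albumin after surgery is likely to be related to the value before it. A two-sample test on follow-up values leaves that predictable variation in the error term and ignores any chance imbalance at baseline. A test on change scores does use the baseline, but with a fixed coefficient of one, which is too large whenever r is below 1 (equal variances). The non-parametric alternative has no baseline term either.

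What is at stake is the width of the confidence intervals, and the power, for outcomes that the protocol presents as part of its hypothesis. The plan itself treats preoperative nutrition as relevant: Subgroup analysis divides patients by preoperative NRS2002 score. Yet the stated between-arm test leaves it out.

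**Working it through.** **The plan's own figure.** The protocol states no sample size, standard deviation, target difference or power for any nutritional outcome, so there is no such figure to reproduce. Its only sample size, 416 per group, is for reflux gastritis. It does not follow from its stated inputs: 8% against 12%, 80% power and two-sided 5% need 882 per arm, or 882/0.85 = 1038 after 15% drop-out. That is a separate matter. Here 416 serves only to show the scale of the evaluable sample: 416 × 0.85 = 353.6, taken as 353 per arm.

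**Inputs.** The test for continuous variables is from Statistical analysis, the laboratory schedule from Table 1, and the group size and drop-out from Sample size. The correlation r between preoperative and follow-up values is not in the documents; 0.3, 0.5 and 0.7 are assumed.

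**Formulas.** Take equal variances and equal r in the two arms, and set the variance of the treatment difference from a t-test on follow-up values to 1. Then:
- t-test on change scores: 2(1 − r)
- ANCOVA on the preoperative value: 1 − r²
- patients the t-test would need, relative to ANCOVA: 1/(1 − r²) for follow-up values, and 2(1 − r)/(1 − r²) = 2/(1 + r) for change scores

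| Assumed r | Change-score variance | ANCOVA variance | ANCOVA against follow-up values | ANCOVA against change scores |
|---|---|---|---|---|
| 0.3 | 1.40 | 0.91 | 1/0.91 = 1.10 | 2/1.3 = 1.54 |
| 0.5 | 1.00 | 0.75 | 1/0.75 = 1.33 | 2/1.5 = 1.33 |
| 0.7 | 0.60 | 0.51 | 1/0.51 = 1.96 | 2/1.7 = 1.18 |

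The gain is therefore 10%, 33% and 96% against follow-up values, and 54%, 33% and 18% against change scores. The better of the two unadjusted t-tests is the one on follow-up values when r is below 0.5 and the one on change when r is above it. Against whichever is better, the gain is 10%, 33% and 18%. At r = 0.2 the ANCOVA variance is 0.96, a gain over follow-up values of only about 4%.

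**Power, as an illustration.** With 353 evaluable patients per arm, a true difference of 0.2 SD (assumed) and two-sided 5%, a t-test on follow-up values has 75.7% power. ANCOVA has 79.5%, 86.6% and 96.1% at r = 0.3, 0.5 and 0.7.

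These factors are for t-tests. The documents give nothing from which to size the gain over a rank test.

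**The case against.** The strongest reply is that nothing here is wrong. Allocation is randomized 1:1, so an unadjusted t-test is unbiased and keeps its type I error. The sentence in Statistical analysis is a condensed list of defaults by variable type. It also covers operating time, blood loss, hospital stay and cost, which have no baseline, and it does not rule out adjustment. Covariates are often left to a statistical analysis plan. The trial is sized on reflux gastritis, so no power claim for nutrition is undermined.

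Most of this stands, and it limits the point to efficiency on secondary outcomes. It does not remove the point. The article names a method, that method has no baseline term, and a method at least as precise in large samples is available from assessments already scheduled.

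Four stronger readings are tempting, and the documents do not support them:
- **That the nutritional comparison is biased or invalid.** Randomization protects the t-test. The article also removes patients after randomization, under Elimination criteria, Uniformity in surgical performance and Outcome measures (recurrence). That can upset comparability, but it is a different problem and baseline adjustment does not cure it.
- **That the trial forgoes the equivalent of nearly twice its patients.** The 96% needs r = 0.7 and a t-test on follow-up values. If change scores are meant, the figure at the same r is 18%.
- **That every nutritional measure has a baseline.** Table 1 supports this only for laboratory tests as a group. For individual analytes it is a reasonable inference; for BMI and appetite the table is silent.
- **That half of the trial's main question is affected.** Nutrition is in the hypothesis, but Outcome measures ranks it as secondary.

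**Conclusion.** The point holds as one of lost precision. The stated analysis of continuous outcomes takes no account of preoperative values that the schedule provides for the laboratory nutritional measures. Validity and the primary comparison are not affected.

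For assumed r between 0.3 and 0.7 the loss is equivalent to about 10% to 96% more patients if follow-up values are tested, and about 54% down to 18% if change scores are tested. It is small for weakly correlated markers. These sizes rest on the assumed r, on equal variances and equal r in the two arms, and on the preoperative laboratory panel including the analytes listed as outcomes. The direction does not depend on r: in large samples ANCOVA is no less precise than either t-test. The change is worth making because it is nearly free.

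**What to change.** Replace the default test for the continuous laboratory nutritional measures, and for BMI if it is recorded preoperatively. Analyse each by ANCOVA at one named visit, or by a mixed model over the scheduled visits, with the preoperative value of the same measure as covariate. Report the adjusted mean difference with its 95% CI, and keep the t-test as an unadjusted check. The existing tests can stay for continuous outcomes with no baseline, such as operating time and blood loss.

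The cost is a change of wording in the analysis plan, made before the arms are compared, and one degree of freedom per analysis for the covariate in the single-visit model. It needs no extra patients, visits or assays and leaves the sample size as it is. It should be confirmed that the preoperative panel contains the analytes named as outcomes.
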